# Intermittent theta-burst stimulation combined with physical therapy as an optimal rehabilitation in Parkinson’s disease: study protocol for a randomised, double-blind, controlled trial

**DOI:** 10.1186/s13063-023-07425-7

**Published:** 2023-06-16

**Keywords:** Intermittent theta-burst stimulation, Parkinson’s disease, Physiotherapy, Randomised controlled trial

## Abstract

**Background:**

First-line rehabilitative strategies to improve motor deficits are based on functional training (physical or occupational therapy), which has been demonstrated to facilitate neural reorganisation. Accumulating evidence suggests that non-invasive brain stimulation techniques, such as repetitive TMS (rTMS), may enhance neuroplasticity, thereby facilitating neural reorganisation and recovery from Parkinson’s disease. Evidence also shows that intermittent theta-burst stimulation (iTBS) can improve motor function and quality of life in patients by promoting the excitability and neural remodelling of cerebral cortex. We aimed to combine iTBS stimulation with physiotherapy to improve the rehabilitation effect compared to physiotherapy alone in patients with Parkinson’s disease.

**Methods:**

This randomised, double-blind clinical trial will enrol 50 Parkinson’s disease patients aged 45–70 years with Hoehn and Yahr scale scores of 1–3. Patients are randomly assigned to either the iTBS + physiotherapy or sham-iTBS + physiotherapy group. The trial consists of a 2-week double-blind treatment period and a 24-week follow-up period. iTBS and sham-iTBS will be administered twice daily for 10 days based on physiotherapy. The primary outcome will be the third part of Movement Disorders–Unified Parkinson’s Disease Rating Scale (MDS-UPDRS III) from the baseline to the first 2 days following completion hospitalised intervention. The secondary outcome will be 39-item Parkinson’s Disease Questionnaire (PDQ-39) at 4 weeks, 12 weeks and 24 weeks after intervention. Tertiary outcomes are clinical evaluations and mechanism study outcomes such as NMSS, 6MWD, 10MT, TUG, BBS, MRI, and EEG, the length of time between the drug needs to be adjusted when symptoms fluctuate.

**Discussion:**

The aim of this study is to demonstrate that iTBS can promote overall function and quality of life in Parkinson’s disease patients using physiotherapy and that this efficacy may be associated with altered neuroplasticity in exercise-related brain regions. The iTBS combined with physiotherapy training model will be evaluated during a 6-month follow-up period. With significant improvement in quality of life and motor function, iTBS combined with physiotherapy can be considered as a first-line rehabilitation option for Parkinson’s disease. The potential of iTBS to enhance neuroplasticity in the brain should have a more positive impact in increasing the generality and efficiency of physiotherapy, improving the quality of life and overall functional status of patients with Parkinson’s disease.

**Trial registration:**

Chinese Clinical Trial Registry ChiCTR2200056581. Registered on 8 February 2022.

**Supplementary Information:**

The online version contains supplementary material available at 10.1186/s13063-023-07425-7.

## Background

Parkinson’s disease (PD) is the second most prevalent age-related, progressive, neurodegenerative disorder, with both motor and non-motor symptoms that substantially impact the quality of life and economic burden of older adults [1, 2]. The clinical features of PD include motor [3, 4] and non-motor symptoms. Gait and posture disorders remain the most discriminating features of the pathology [5, 6] and all the disorders can disable patients and severely limit their quality of life [6-8]. Although non-motor symptoms can reduce a patient’s quality of life, treatment of PD primarily focuses on improving motor symptoms [9].

One review showed that many studies have been undertaken to investigate the effectiveness of repetitive transcranial magnetic stimulation (rTMS) for PD patients with motor dysfunction [10]. rTMS therapy has been reported to be an effective treatment for motor symptoms of PD, and multi-session high frequency (HF) stimulation on M1 can be an optimal stimulation protocol. rTMS can directly affect cortical excitability at the site of stimulation and may also affect the excitability of other brain regions associated with the site of stimulation through the cortico-striatum-thalamus-cortical circuitry. It has been suggested that rTMS might influence cortical excitability and, thus, brain function and can be applied in bursts of HF (≥ 5 Hz) or continuous trains of low frequency (LF) (≤ 1 Hz). In general, the current generated by the magnet through the time-varying magnetic field acts on the cerebral cortex, producing neuroplasticity changes similar to long-term enhancement (LTP) or depression. HF-rTMS can enhance excitability in the cortex, and LF-rTMS can reduce excitability [11-13].

Theta-burst stimulation (TBS) is another form of rTMS protocol with HF and low‐intensity stimulation, which may facilitate induction of plasticity mechanisms [14], and uses a short stimulation duration, low stimulation pulse intensity, and a possibility to improve rTMS efficiency [15]. When TBS is delivered continuously (cTBS), it decreases cortical excitability; whereas intermittent theta-burst stimulation (iTBS) increases cortical excitability [16]. Because TBS may have fewer adverse effects, such as seizures, impairment of hearing and cognition function [17], and shorter time of single intervention (within several minutes) compared with traditional rTMS, in recent years, an increasing number of studies have begun to explore the therapeutic effect of TBS on motor and non-motor symptoms in patients with PD (PWP) [18-27].

Physiotherapy has been advocated for PD patients. There is substantial evidence that physical therapy can be beneficial in improving walking, muscle strength and balance or reducing falls [28-30]. Thus, physiotherapy (PT) aims to protect, enhance or restore movement and bodily functions that are impaired or threatened by disease, injury and disability. Training techniques include active exercise modalities such as aerobic endurance and muscle strength training, cueing techniques and cognitive motor strategies to improve limitations in fitness, gait, balance, posture and transfer [31]. The focus of these studies has been on motor difficulties such as gait impairment and balance problems. There are numerous studies showing that rTMS combined with rehabilitation therapy has a good effect on stroke, schizophrenia and other diseases, especially in the improvement of upper limb motor function [32], dysphagia [33], aphasia function [34] and cognitive function [35] after stroke.

This trial aims to estimate the efficacy and effectiveness of iTBS combined with physiotherapy. We aim to explore the application of iTBS and new PT rehabilitation programmes in Parkinson’s disease, which may provide evidence for new rehabilitation models with higher economic benefit ratio of PD.

## Methods

### Study design

The study will be a double-blind, randomised, placebo-controlled trial. This protocol is reported in accordance with the Standard Protocol Items: Recommendations for Interventional Trials guidelines [36]. We hypothesise that iTBS combined with physiotherapy is more efficient and effective than physiotherapy alone for the treatment of PD.

The protocol adheres to the guidelines outlined by the Helsinki Declaration and Measures for Ethical Review of Biomedical Research Involving Humans and has been approved by the Ethics Committee of Beijing Hospital, Capital Medical University. The trial will be conducted under the supervision of the Department of Scientific Research Management of the Beijing Rehabilitation Hospital, Capital Medical University. All participants provided written informed consent before participation. This study was registered in the Chinese Clinical Trial Registry (ChiCTR2200056581). The total study duration for one patient will be 26 weeks, with baseline evaluation (T0) for 2 days and an intervention time of 10 days, and efficacy will be assessed after intervention for 2 days (T1), 4 weeks (T2), 12 weeks (T3) and 24 weeks (T4) (Fig. 1).

**Fig. 1 Fig1:**
[figure not shown]
Study design flow chart. The 26-week study will include baseline evaluation (T0) for 2 days, an intervention time of 10 days, and efficacy will be assessed after intervention for 2 days (T1), 4 weeks (T2), 12 weeks (T3) and 24 weeks (T4)

### Participants

PD patients will be recruited through the outpatient clinic of Beijing Rehabilitation Hospital, Capital Medical University, as well as through the hospital website. Recruitment will continue in 2023, and participants will be randomly assigned (at a 1:1 ratio) to the iTBS + PT or sham-iTBS + PT group, with 25 participants in each group. Patients with appointments will first be screened by telephone to determine their qualification, and then to go to the outpatient clinic to conduct on-site screening. The recruitment and intervention of the trial group will be carried out in the Beijing Rehabilitation Hospital, Capital Medical University. The follow-up evaluation at each time point will be carried out online by the electronic data capture (EDC) system.

All participants must sign a written informed consent form. Participation is voluntary and patients can leave the study at any time. All of the data will be anonymised. We will establish multiple communication channels to maintain close contact with participants.

### Inclusion criteria

Conformity with the diagnostic criteria of idiopathic PD according to the 2015 Movement Disorder Society (MDS) criteria [37]Age of 45–70 years and primary school education level and abovePatients that are classified as 1–3 according to the Hoehn and Yahr scale [38, 39]Patients prescribed a type and dosage of drugs used for more than 2 weeks that has not been adjusted in the short termThose who can walk without assistance (including assistive devices) and need no help from others in daily lifeSubjects that consciously abide by the ward management regulations and epidemic prevention requirements and pass the admission and epidemic prevention screening as requiredThose who voluntarily sign the informed consent form and confirm that they will be able to complete the treatment

### Exclusion criteria

Patients who do not take their medication under the guidance of a doctor or cannot take their medication regularlySubjects with visual or hearing impairment, cardiovascular or cerebrovascular diseases, and respiratory system diseasesThose with secondary Parkinson syndrome or Parkinsonism-plus syndrome caused by drugs, encephalitis, metabolic diseases, stroke, carbon monoxide poisoning, brain tumours or other neurologic degenerative diseasesPatients who are unable to cooperate throughout the study because of drug abuse or poor adherence according to the investigators’ judgementSubjects who have participated in other studies in the 2 weeks prior or are currently participating in other clinical trialsPregnant or lactating womenInsufficient compliancePatients with cognitive, motor, speech and other impairments caused by other nervous system diseasesA history of epilepsy or other contraindications to transcranial magnetic stimulationSubjects who are unwilling or unable to participate in MRI examinations (such as those with claustrophobia or non-MRI-compatible implants in the body)Severe cognitive impairment or audio-visual impairmentSerious concomitant diseases such as heart, lung, liver and kidney insufficiencyThose who are participating in other clinical trials or are going to undergo DBS surgery or participate in other clinical trials in the next 12 monthsPatients who are not willing to sign the informed consent formThose who do not meet or do not cooperate with the requirements of epidemic prevention

### Dropping criteria

Patients who do not finish the training among the two groupsAggravation of the disease that will require a replacement of drugs

### Randomisation

A researcher who is not involved in the assessments or stimulation will perform the randomisation of the patients. We will use the complete randomisation function of SPSS 26.0 statistical software (IBM, Chicago, IL, USA) to obtain a table of random numbers, and SPSS Visual Binning function has programmed its system to pull from spreadsheets of random numbers to determine assignment. There is no human involvement, and the process is fully concealed from both study investigators and prospective participants until the study arm is assigned.

### Blinding

Patients and clinical researchers will be kept unaware of the course of treatment until the study is completed. The doctors who implement the iTBS and the researchers in charge of randomising the group will know the packet information but will not communicate with the patients. To ensure double blinding, we will instruct patients to not discuss their treatment groups with other patients or staff. When serious adverse events are encountered that require immediate unblinding, the person in charge of the scientific research management department, the project leader of the data management department and the statistician will do so jointly and record the unblinding process in detail. Unblinding will only reveal the kind of patient treatment with a random number and does not affect the blinding of other participants.

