**Fig. 2 Fig2:**
[figure not shown]
The iTBS + PT group

ITBS (Magstim Rapid^2^, Whitland, UK) will use standard, internationally approved parameters: 80% resting movement threshold (RMT) stimulation intensity; triplet 50 Hz bursts, repeated at 5 Hz for 2 s on and 8 s off, 10 times; 600 pulses per session; for a total duration of 3 min 20 s.

For the RMT measurement, the centre of the figure-of-eight coil is aimed at the base of the scalp of the cerebral cortex movement area, the patient is told to completely relax, and the transcranial magnetic stimulation output intensity is gradually adjusted. Ten consecutive single stimulations can induce five movement evoked potentials with an amplitude greater than 50 V minimum stimulation intensity; or 10 stimulations, at least five times, will cause the minimum intensity of the left thumb muscle contraction [40]. The frameless stereo optical tracking and navigation system is used for positioning. We will conduct dynamic real-time monitoring throughout the treatment process to ensure the accuracy of the target. To obtain stimulation target M1, all participants will undergo MRI brain scans prior to the study: the target is a spherical image centred on the centre point of the M1 surface in a standard brain template based on T1-weighted anatomical magnetic resonance structural images. The target of M1 is transformed into an image of the brain structure of each individual, which is then introduced into a frameless neuronavigation system (Brainsight, Brainbox Ltd, Cardiff, UK).

The coil remains horizontal and tangential to the skull, pointing forward, with its centre point overlapping the target of M1 [41, 42]. Initial treatment consists of twice-daily sessions (on week days; i.e., five sessions a week).

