**Fig. 3 Fig3:**
[figure not shown]
The sham-iTBS + PT group

If the patient suffers an unbearable headache, we will reduce the intensity of the intervention to 40 Hz or below; if more serious side effects occur, we will choose the parameters suitable for the patient’s tolerance or stop the treatment altogether. Doctors and therapists will report adverse events during the intervention in writing to the study group in the EDC system. Falls, injuries and harmful adverse events will also be reported due to the rules and regulations of Beijing Rehabilitation Hospital, Capital Medical University.

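### The no-contact rule for arm-aware iTBS doctors conflicts with symptom-driven stimulation changes and adverse-event reporting, leaving tolerability data open to arm-aware capture

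*Protocol article*

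**What the plan says.** All references are to the protocol article.

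- **Blinding.** "Patients and clinical researchers will be kept unaware of the course of treatment until the study is completed". The exception is stated next: "The doctors who implement the iTBS and the researchers in charge of randomising the group will know the packet information". The safeguard attached to that exception is in the same sentence, which says that these people "will know the packet information but will not communicate with the patients". No limit or exemption is given.
- **Sham-iTBS + PT group, text on side effects.** "If the patient suffers an unbearable headache, we will reduce the intensity of the intervention to 40 Hz or below". For more serious effects, "we will choose the parameters suitable for the patient’s tolerance or stop the treatment altogether". The role that takes these steps is not named.
- **Same place, on reporting.** "Doctors and therapists will report adverse events during the intervention in writing to the study group in the EDC system". The stimulating doctors are neither named nor excluded.
- **iTBS + PT group, threshold measurement.** "the patient is told to completely relax, and the transcranial magnetic stimulation output intensity is gradually adjusted". The speaker is not identified.
- **Data collection.** Raters of the listed assessments are blinded. Adverse-event recording is described separately, after that statement.
- **Data monitoring.** A neurologist on the monitoring board assesses, manages and classifies all adverse events. Whether this person is blinded is not stated.

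**The concern.** The plan protects the blind at the stimulation sessions by keeping arm-aware doctors from communicating with patients. Yet headache and tolerance are felt by the patient, and they must reach whoever sets the device before a change or stop can follow. The article names no blinded intermediary for this. It also does not keep the operators out of adverse-event reporting.

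These are subjective judgements. Someone who knows the coil is sham may give a complaint less weight than someone who knows it is active. Two things are at stake:

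- the comparison of tolerability between arms;
- the pattern of stops. The Dropping criteria list patients who do not finish training, and the Statistical analysis section ties the per-protocol analysis to non-receipt of the intervention for reasons that include adverse effects and adherence.

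**Working it through.** The plan states no figure on this point, so the check is mainly a comparison of passages.

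**1. Two readings of the no-communication rule.**

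- *Literal: no communication.* A change made because of unbearable headache needs the complaint to reach the person setting the stimulation. With no relay described, the Blinding section and the side-effects text cannot both be followed as written.
- *Narrow: no disclosure of the allocation.* The literal conflict disappears. But doctors who know the arm may then hear complaints, judge tolerance and file adverse events, and nothing in the text controls how they do so.

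Both readings leave something to correct: the wording under the first, ascertainment under the second.

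**2. Do other safeguards close the gap?**

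- Blinded raters (Data collection) cover the efficacy and functional assessments listed there, not adverse events.
- The board neurologist (Data monitoring) classifies events already reported. A complaint that is never entered does not reach that step.
- The threshold-measurement instruction adds little, because the speaker is unnamed and being told to relax reveals nothing about the arm.

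**3. Exposure.** Inputs are twice-daily stimulation (iTBS + PT and sham-iTBS + PT groups), 10 consecutive days (Intervention) and 50 patients (Sample size).

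- Sessions per patient: 2 × 10 = 20.
- Sessions in total: 20 × 50 = 1,000.

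This is an upper bound on sessions given by someone who knows the arm, since the iTBS + PT section also uses weekday wording. It is not a count of biased reports.

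**4. Sensitivity of the tolerability comparison.** Each arm has 25 patients (Participants). One patient whose event is recorded in one arm but would have been missed in the other moves the reported difference by 1/25 = 4 percentage points. As an assumed range, since the documents give no event rates:

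| Patients captured differently | Shift in reported difference |
|---|---|
| 1 | 1/25 = 4 points |
| 2 | 2/25 = 8 points |
| 3 | 3/25 = 12 points |

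**5. Sensitivity of the per-protocol set.** The planned 12% dropout is 0.12 × 25 = 3 patients per arm. A single stop influenced by knowledge of the arm, if it removes the patient from the per-protocol set, is therefore one third of that allowance.

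**The case against.** The strongest reply is that the rule is a loosely worded ban on revealing the allocation. The next sentence in the Blinding section tells patients not to discuss their group, which fits that meaning, and ordinary contact about symptoms would then be allowed. The side-effects text speaks only of doctors, therapists and an unspecified we. Patients are treated in hospital, so ward doctors or physiotherapists could be the reporters, and a blinded person could relay complaints. An operator who knows which coil is fitted is also hard to avoid with a sham coil. Tolerability is not listed as a primary, secondary or tertiary outcome.

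Much of this stands. A reader might infer that the blinding safeguard is bound to fail. The documents do not show that, because they never identify the reporters or decision-makers as the operators.

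A reader might also infer that patients will learn their arm and that the self-reported PDQ-39 is compromised. That is not supported either. The sham coil is described as simulating sound and touch, and follow-up evaluation is online through the data capture system at 4, 12 and 24 weeks.

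What the reply does not answer is that, on its own reading, the text still lets people who know the arm be the first to capture symptoms.

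**Conclusion.** The point holds in a limited form. The Blinding section and the side-effects text need reconciling, and as written the first capture of adverse events and tolerance is not protected from knowledge of the arm. The bias would fall on the tolerability comparison and, through stops, on the secondary per-protocol analysis. Its size is unknown. The arithmetic shows only that, at 25 per arm, a few differently handled reports would be visible.

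The conclusion assumes that the operators are at least sometimes among the reporting doctors, which the text permits but does not state. The effect of stops further assumes that a patient whose stimulation is stopped leaves the per-protocol set. The primary outcome is not directly threatened, because MDS-UPDRS III is rated blind. This should be corrected, but it does not undermine the main efficacy claim.

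**What to change.** 1. In the Blinding section, replace the no-communication rule with limited, scripted contact that is identical in both arms and never discloses the allocation. Align the side-effects text with it.
2. Add a standard adverse-event and tolerance question, asked and entered in the data capture system once daily at the existing physiotherapy session, in addition to any operator report. Stimulation is twice daily and physiotherapy once, so the question should cover the time since the previous physiotherapy session.
3. Have it asked by a therapist confirmed to be unaware of the arm. The Blinding section does not list physiotherapists among those who know the allocation, but no passage says they are blinded, so the sponsor must confirm this.
4. Record for each report whether the reporter knew the arm, and state whether the neurologist who classifies events is blinded.
5. Optionally, ask patients at T1 to guess their arm.

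The sponsor should decide and state who makes parameter changes or stops; no rule is proposed here.

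The cost is protocol wording, a few data fields and a few minutes of therapist time per day, with no extra visits. The Trial status section says recruitment is ongoing, so patients still to be enrolled could benefit once the ethics committee approves the amendment.
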